#### **8.3.5 Subgroup analyses**

To explore differences in the evolution between pregnant and non-pregnant women, subgroup analysis for the primary and secondary outcomes will be performed. Other potential subgroup analysis will compromise healthy and unhealthy subgroups based on BMI, glycemia and blood pressure at baseline to assess their evolution and identify the subgroups with larger and smaller effects on the primary and some secondary outcomes.

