Based on the above and considering a 95% level of significance (one-sided p-value), a power of 91% to detect the effect size is achieved. The possibility of an entire cluster withdrawal was also considered. Based on the previous parameters and 1 cluster dropped (2 intervention clusters and 3 comparison clusters or vice versa), a power of 85% would be reached.

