### 8.3 Statistical methods

#### 8.3.1 Analysis populations

The analyses will be conducted based on the intention-to-treat principle. A probability of <0.05 will be considered statistically significant for all tests. All analyses will be conducted using STATA (Release 16/SE. College Station, TX: StataCorp LP) by ITM's staff.

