#### 8.3.3 Primary analysis

After the termination of the study, the primary and secondary outcomes will be evaluated for normality by the Kolmogorov-Simonov test and visual inspection of histograms. For the primary ordinal outcome (Healthy lifestyle Questionnaire Score), the impact of the intervention program

between baseline and follow up of the 2 groups (intervention and comparison group) will be assessed by using random effect (clusters) linear mixed models for repeated measurements.

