#### **8.3.6 Multiplicity and Missing Data**

Bonferroni's p-value correction for multiple comparisons will be considered. This will be performed by dividing the total p-value (0.05) by the final number of outcomes used in the final analyses (primary + secondary outcomes). Moreover, as mentioned the analysis will be performed under the ITT principle. To avoid and/or decrease missing data, particularly in the questionnaires, health professionals will be asked to revise the questionnaires for completeness right after the participants have filled them up. In the case of missing answers, participants will be asked to provide an answer to the questions. Nonetheless, the primary and secondary outcomes will be assessed by a linear mixed model, which is a model that can handle missing values by using maximum likelihood estimations.

Interim analyses will be performed for the primary and secondary parameters will be assessed after the completion of each set of measurements (~ 6 months) by quantifying the % of women improving dietary habits and physical activity levels and categorizing into different levels of improvement, % of women with a BMI <25 kg/m^2, % of pregnant women gaining the correct amount of weight based on their pre-pregnancy BMI, % of women with normal glycemia levels, and % of women with normal blood pressure. Also, evaluation of intervention program indicators will be performed though summarizing the % of trained peer educator and health professionals, % of optimal data available for key indicators and the % of patients who have withdrawn the IC.

Moreover, to determine whether it is feasible and acceptable to complement the intervention program with community based-strategies, the Likert scale will be summarized by frequency distribution and percentages, this will be carried out during the first year of intervention program.

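### The subgroup section sets out to find larger and smaller effects but plans no arm-by-subgroup interaction and no criterion for calling effects different, and the multiplicity rule does not count subgroups

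*Combined protocol and SAP*

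**What the plan says.** Section 8.3.5 has two parts. The first concerns pregnancy: "To explore differences in the evolution between pregnant and non-pregnant women, subgroup analysis for the primary and secondary outcomes will be performed". The second describes further possible splits into "healthy and unhealthy subgroups based on BMI, glycemia and blood pressure at baseline", with the aim "to assess their evolution and identify the subgroups with larger and smaller effects on the primary and some secondary outcomes". That makes four factors. No cut-offs for healthy and unhealthy are given there.

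The primary outcome "will be assessed by using random effect (clusters) linear mixed models for repeated measurements" (section 8.3.3), and section 8.3.4 extends the same model to the secondary outcomes. Neither section names a subgroup term. Section 8.3.1 sets the threshold: "A probability of <0.05 will be considered statistically significant for all tests". Section 8.3.6 says a Bonferroni correction will be considered, "dividing the total p-value (0.05) by the final number of outcomes used in the final analyses (primary + secondary outcomes").

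The opening of section 8 promises a binding SAP before database lock, but the documents contain no further subgroup method.

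**The concern.** To say that the programme works better in one group of women than in another is a statement about a difference between two between-arm differences. Section 8.3.5 never names that quantity. It speaks of a subgroup's *evolution*, which can be read as change over time inside the subgroup, and of picking out larger and smaller effects, which can be done by setting estimates side by side. Two estimates will differ whether or not the true effects do, so without a test, an interval or a threshold nothing tells the reader when a gap is more than noise.

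A second problem depends on how *evolution* is read. Three of the four factors (BMI, glycemia, blood pressure) are also secondary outcomes. Women chosen because a baseline value was high will on average be lower on that same variable later, with no programme effect. Change within the subgroup would show this as improvement.

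What is at stake is any statement about who benefits more or less. The overall comparison of the arms is not in question.

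**Working it through.** **Inputs from the documents.** Three centres per arm (3.1); 40 analysed per centre, so 120 per arm, with SD 7 and ICC 0.1 (8.4); design effect 6 points (4.3); four factors (8.3.5).

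**Assumed, because the documents give no figure.** The smaller subgroup holds 50%, 30% or 20% of women; the four factors are independent; one end-of-study comparison; the gap does not vary between centres; normal approximation.

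**1. Reproduce the plan's power.** Design effect = 1 + 39 × 0.1 = 4.9. Effective size = 120 / 4.9 = 24.5 per arm. SE = 7 × √(2/24.5) = 2.00. One-sided power = Φ(6/2.00 − 1.645) = 0.912, against the stated 91%. The inputs are therefore those the plan used.

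**2. Standard error of a subgroup gap.** Let a and b be the subgroup sizes per arm. The gap is the arm difference in one subgroup minus that in the other. Both subgroups sit in the same centres, so the centre effect cancels:

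SE = 7 × √0.9 × √(2/a + 2/b)

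**3. Chance gaps when the effect is identical in all women.** Median absolute gap = 0.6745 × SE. Chance of 3 points or more in one split: p = 2 × [1 − Φ(3/SE)]. Chance in at least one of four: 1 − (1 − p)⁴.

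| Share | a, b | SE | Median gap, one split | p | At least one of four |
|---|---|---|---|---|---|
| 50% | 60, 60 | 1.71 | 1.2 | 0.080 | 28% |
| 30% | 36, 84 | 1.87 | 1.3 | 0.109 | 37% |
| 20% | 24, 96 | 2.14 | 1.4 | 0.162 | 51% |

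A simulation of 6,000 trials per setting, in which subgroup sizes vary by centre, gave slightly larger values: mean gaps of 1.4, 1.5 and 1.8 points (at the 20% share a median near 1.5), and a gap of 3 points or more in at least one split in 29–55% of trials. The results were similar with a common effect of 0 or 6 points.

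**4. If subgroups were instead judged by separate p-values.** At one-sided 0.05 in each subgroup, as in the power calculation ("considering a 95% level of significance (one-sided p-value"), at least one of the four splits was significant in one subgroup and not in the other in 27%, 36% and 51% of trials under a common 6-point effect, and in 12–16% under no effect.

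**5. What an interaction test would do, for one outcome.** Four tests at 0.05: 1 − 0.95⁴ = 18.5% chance of at least one false alarm. At 0.05/4 = 0.0125 each: 1 − 0.9875⁴ = 4.9%. Two-sided power per test, from Φ(3/SE − 1.96) for a true 3-point gap, is 42%, 36% and 29% at the three shares. Replacing 1.96 by 2.498 (for 0.0125) gives 23%, 19% and 14%. For a true 6-point gap, power at 0.05 is 94%, 89% and 80%. With six centres the normal approximation is optimistic.

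**6. Regression to the mean, under the within-subgroup reading only.** Expected fall = (1 − ρ) × SD × φ(z)/[1 − Φ(z)]. Assume systolic mean 120, SD 15 and visit correlation 0.6 (none in the documents). Women at or above 130: z = 0.667, fall = 0.4 × 15 × 0.3194/0.2525 = 7.6 mmHg. At or above 140: z = 1.333, fall = 6 × 0.1640/0.0912 = 10.8 mmHg. No programme effect is involved.

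**The case against.** The section is exploratory: it says so for pregnancy and calls the other splits only potential. A reader might infer a decision rule that always declares a better subgroup. The documents do not support that. Any table of subgroup estimates shows unequal numbers, and section 8.3.5 attaches no action or claim to the ordering. What stands is that it states an aim of identifying differing effects and gives no means of doing so.

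A reader might also infer that uncontrolled before-after tests will be run in the unhealthy groups. No section plans such a test. Sections 8.3.3 and 8.3.4 describe a comparison of the two arms, and the word effects in 8.3.5 most naturally means the same comparison. In that comparison regression to the mean largely cancels, because it is expected in both arms. Nor does it directly touch the questionnaire score, which is not a selection variable. The point holds only if *evolution* is taken as within-subgroup change, which the wording permits.

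A third inference, that the programme would be targeted by subgroup, has no basis: section 2 plans to make the programme as a whole available.

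The sizes can also be challenged. The planned model uses baseline and repeated measurements. If baseline adjustment at a correlation of 0.5–0.7 (assumed) scaled the SE by √(1 − ρ²), that is by 0.87–0.71, the 28–51% would become 16–36% at 0.5 and 6–19% at 0.7. Interaction power would rise too, to 37–52% and 50–69% for a true 3-point gap at 0.05. This reduces the problem without removing it.

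Finally, the promised SAP could add the test. That makes it the natural place for the correction, but it does not supply what the present text lacks.

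**Conclusion.** The point holds as a defect in an exploratory section. Followed as written, section 8.3.5 offers no way to tell effect modification from chance. With an identical effect in all women, one split has a median chance gap of about 1.2–1.5 points, and at least one of four reaches 3 points in about 28–51% of trials. These figures use the plan's SD, ICC and numbers analysed, and rest on assumed shares of 20–50%, independent factors and no gain from baseline adjustment. The four-split figure describes the most extreme split, not a typical one. The blood pressure figures illustrate a mechanism under assumed inputs and apply only to within-subgroup change.

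The primary conclusion and its stated power are not affected by this point.

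**What to change.** Rewrite section 8.3.5, or settle it in the SAP before database lock, to say that:

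- Effect modification by baseline pregnancy status, BMI, glycemia and blood pressure is assessed by the arm-by-time-by-subgroup interaction in the same mixed model, at a named visit, with subgroup cut-offs and the outcomes to be examined fixed in advance.
- The between-arm difference in each subgroup and the interaction estimate are reported with confidence intervals, using a small-sample degrees-of-freedom correction because there are only six centres.
- No subgroup is described as having a larger or smaller effect on the basis of ranking or within-subgroup change alone.
- Results are labelled hypothesis-generating unless the interaction is significant after correction for the number of splits and outcomes examined. Correcting for the four splits alone controls the error for one outcome only.

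The cost is wording and one set of interaction terms per split, with no new data. The downside is power: about 29–42% for a true 3-point gap at 0.05 without baseline adjustment, and about 14–23% after correction for four splits. Fewer subgroup statements will be possible.

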#### **8.3.6 Multiplicity and Missing Data**

Bonferroni's p-value correction for multiple comparisons will be considered. This will be performed by dividing the total p-value (0.05) by the final number of outcomes used in the final analyses (primary + secondary outcomes). Moreover, as mentioned the analysis will be performed under the ITT principle. To avoid and/or decrease missing data, particularly in the questionnaires, health professionals will be asked to revise the questionnaires for completeness right after the participants have filled them up. In the case of missing answers, participants will be asked to provide an answer to the questions. Nonetheless, the primary and secondary outcomes will be assessed by a linear mixed model, which is a model that can handle missing values by using maximum likelihood estimations.

Interim analyses will be performed for the primary and secondary parameters will be assessed after the completion of each set of measurements (~ 6 months) by quantifying the % of women improving dietary habits and physical activity levels and categorizing into different levels of improvement, % of women with a BMI <25 kg/m^2, % of pregnant women gaining the correct amount of weight based on their pre-pregnancy BMI, % of women with normal glycemia levels, and % of women with normal blood pressure. Also, evaluation of intervention program indicators will be performed though summarizing the % of trained peer educator and health professionals, % of optimal data available for key indicators and the % of patients who have withdrawn the IC.

Moreover, to determine whether it is feasible and acceptable to complement the intervention program with community based-strategies, the Likert scale will be summarized by frequency distribution and percentages, this will be carried out during the first year of intervention program.

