### 4.3 Sample size

The present study is based on a three-level hierarchical design where two groups of 3 healthcare centers (matched in population size and geographical area, urban/rural) will be randomized to the intervention and comparison group, and healthcare workers within the same cluster provide the intervention allocated to the participants

The sample size will be based on the expected differential change in the primary outcome of the study (healthy lifestyle score) determined by the questionnaire developed and validated in India by Dubasi and co-workers to assess the adherence to dietary and physical activity advice for weight control in lifestyle-related diseases. The questionnaire's total score ranges between 14-65 points, a lower score indicates poor adherence to a healthy lifestyle, while a higher score indicates good adherence.

In this cRCT, 1 group of 3 healthcare centers will be randomly allocated to the intervention group and the other group of 3 healthcare centers to the comparison group. A comparable study measuring also lifestyle behavior changes as primary outcome, and using a similar score scale has reported a differential improvement from baseline to follow-up after 35 weeks of 20% between intervention and comparison groups. Also, literature has reported intra-class correlation (ICC) coefficients for interventions concerning dietary and physical activity improvements range in between 0.007-0.3.

Based on this previous evidence and the demographics of our study setting, the following assumptions have been used to approximate a power calculation estimate. This calculation was done using STATA version 16 for a cluster-randomized design assuming a realistic number of participants sample from each healthcare center whereby the following parameters were considered:

- 48 participants per cluster (144 participants per intervention program)
- Improvement of 12% in the lifestyle questionnaire score between intervention and comparison group (+ 6 score points)
- Effect size of 0.7 (score of the average person in the experimental group is 0.7 standard deviations above the average person in the comparison group, thus surpasses the scores of 69% of the comparison group).
- ICC of 0.1
- 20% loss to follow up and no attrition expected

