### 8.2 Variables of interest

After the termination of the study, the primary and secondary outcomes will be evaluated for normality by the Kolmogorov-Simonov test and visual inspection of histograms. In case of non-normally distributed outcomes, log transformation and non-parametric tests will be considered.

The primary outcome (healthy lifestyle questionnaire score) will be a variable with ordinal values ranging between 14-65 points. The secondary outcomes of anthropometrics (weight [kg], height [m], BMI [kg/m^2], waist circumference [cm]), clinical indicators (glycemia [mg/dL] and blood pressure [mmHg]), and total MET-min/week and kcal/week collected by the physical activity questionnaire will be variables with continuous values. Only the outcome of diet diversity will be provided as an ordinal variables ranging from 0-10.

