#### **8.3.4 Secondary and tertiary analysis**

For secondary ordinal and continuous outcomes (anthropometric, clinical, questionnaires, etc.), exploratory analysis using the same method of linear mixed models for repeated measurements.

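### Section 8.3.6 may divide the primary outcome's alpha by 8 to 11, which the sample size did not allow for: power would be about 65–69%, not the stated 91%

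*Combined protocol and SAP*

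**What the plan says.** Four places in the combined protocol and SAP bear on the threshold for the primary outcome.

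- Section 8.3.6 opens conditionally: "Bonferroni's p-value correction for multiple comparisons will be considered". The method is then given as "dividing the total p-value (0.05) by the final number of outcomes used in the final analyses (primary + secondary outcomes".
- Section 8.3.4 describes the secondary outcomes as "exploratory analysis using the same method of linear mixed models for repeated measurements".
- Section 8.3.1 sets a general rule: "A probability of <0.05 will be considered statistically significant for all tests". It does not say whether tests are one- or two-sided.
- Section 4.3 sizes the trial for "Improvement of 12% in the lifestyle questionnaire score between intervention and comparison group (+ 6 score points", and reports, "considering a 95% level of significance (one-sided p-value), a power of 91% to detect the effect size is achieved". Section 8.4 uses the same one-sided level in all its scenarios. Neither section divides alpha.

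The secondary outcomes are named in sections 2.2 and 8.2. Height is among them ("The secondary outcomes of anthropometrics (weight [kg], height [m"), although Table 1 in section 5.1 schedules it at baseline only.

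**The concern.** With one primary outcome there is no multiplicity to correct for in the primary test, provided it is made on one contrast. Putting that outcome into a family with the secondaries gives most of its alpha to analyses that the plan does not treat as confirmatory. The power calculation never paid for this. If the rule were applied, the trial would be run at a threshold roughly a tenth of the one it was sized for.

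The second difficulty is that the threshold is not settled. The correction is only to be considered, and its divisor depends on how many outcomes are used in the final analyses. From the text alone, an analyst could not say whether a primary p-value of 0.03 is a success. The trial is unblinded (section 4.4), and outcome summaries are produced about every six months (sections 8.3.6 and 9), so the question should be closed before any of those data are seen.

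**Working it through.** **Inputs.** Difference 6 points (4.3). SD 7 and ICC 0.1 (8.4; the ICC is also in 4.3). Three clusters per arm (4.3). 40 evaluable women per cluster, with 48 enrolled to allow for loss (4.3, 8.4). One-sided alpha 0.05 (4.3, 8.4).

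**Reproducing the plan's figure.** I used the normal approximation with a design effect.

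- Design effect = 1 + (40 − 1) × 0.1 = 4.9
- SE = 7 × √(4.9 × 2 / 120) = 2.00
- Difference / SE = 6 / 2.00 = 3.00
- Power = Φ(3.00 − 1.645) = 91.2%, against 91% stated

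With one cluster lost (2 against 3) the same formula gives 85.0%, against 85% stated. It also agrees within 2 percentage points with the 48 cells of the section 8.4 grids that were checked. At two-sided 0.05 it gives 85.1%, so the 91% is the one-sided figure. This is therefore the plan's own formula.

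**Counting the family.** Sections 2.2 and 8.2 together give weight, height, BMI, waist circumference, SBP, DBP, glycemia, MET-min/week, kcal/week and diet diversity: 10 variables. Leaving out height gives 9. Counting blood pressure once gives 8. Counting MET-min and kcal as one physical activity measure gives 7. With the primary added, the divisor k runs from 8 to 11.

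**Power with the divided alpha.** Power = Φ(3.00 − z), where z is the normal quantile for alpha = 0.05/k. For the two-sided column, that alpha is halved before z is taken.

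| k | alpha | one-sided z | power, one-sided | power, two-sided |
|---|---|---|---|---|
| 1 | 0.05 | 1.645 | 91.2% | 85.1% |
| 8 | 0.00625 | 2.498 | 69.2% | 60.4% |
| 9 | 0.0056 | 2.539 | 67.7% | 59.0% |
| 10 | 0.0050 | 2.576 | 66.4% | 57.6% |
| 11 | 0.0045 | 2.608 | 65.2% | 56.4% |

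On the one-sided figures, the chance of missing a true 6-point difference rises from about 9% to between 31% (k = 8) and 35% (k = 11). No count from 8 to 11 reaches the >80% in the synopsis.

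**The case against.** The strongest reply is that section 8.3.6 commits to nothing: the correction is to be considered, and the next sentence only explains how it would be done. This stands, and it makes the power loss conditional. It does not remove the point, because the primary's threshold is then left open.

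Section 8 also says that a binding SAP will be written and finalized before database lock or before any other analysis. That SAP could settle the matter. But the rule it would inherit includes the primary, and the first of those two deadlines falls after the end of the study (section 10), when the six-monthly summaries have already been seen.

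Bonferroni over primary and secondary outcomes is valid and conservative, so false positives are not inflated. This is correct: the cost is power only. Nor do sections 8.3.1 and 8.3.6 strictly contradict each other, since Bonferroni-adjusted p-values could be compared with 0.05. The firm mismatch is between section 8.3.6 and the power calculation.

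Two stronger readings should be resisted.

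- A reader might infer that the trial would probably miss the effect it was sized for. On the plan's formula, detection stays more likely than not, even two-sided. Power falls below one half only if a t reference with 4 degrees of freedom is used for the six clusters (23–29% one-sided for k = 11 to 8). That is a separate issue, which alone takes the undivided figure to about 79%.
- A reader might infer that the divisor wrongly ignores the four follow-up visits, leaving error uncontrolled across them. Section 8.3.3 describes one repeated-measures model, and the interim summaries are percentages with no tests stated. No section plans a separate test at each visit. What is missing is a named contrast, which is a side point here.

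**Conclusion.** The point holds in conditional form. If the correction in section 8.3.6 is applied as described, the stated 91% no longer describes the trial, and the synopsis power is not met. If it is not applied, the 91% is unaffected by this point, but the text still allows two thresholds for the primary that differ by a factor of 8 to 11.

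The size rests on the plan's assumptions of SD 7, ICC 0.1 and 40 evaluable women per cluster, on its normal-approximation formula, and on a divisor of 8 to 11. The documents do not fix the divisor, so the result should be quoted as a range; the figure for 10 or 11 outcomes alone is its unfavourable end.

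**What to change.** State in section 8.3.6, and carry into the SAP, that:

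1. The healthy lifestyle score is the sole primary test. It is made on one prespecified contrast, at the full alpha and the sidedness used in section 4.3, with no Bonferroni division. The sponsor should name the contrast in section 8.3.3; month 24 is one option for it to confirm.
2. Any Bonferroni or Holm correction applies only among the secondary outcomes.
3. Height is not an outcome, and the list of secondary outcomes is fixed before any outcome data are analysed.

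Amend section 8.3.1 to match, including the sidedness. The cost is wording only: no change to sample size, visits or data collection. If the sponsor prefers to keep the primary in the family, sections 4.3 and 8.4 and the synopsis should instead give power of about 65–69% one-sided (56–60% two-sided), with the divisor stated.
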